**Attachment 2: (Continued)**  
Interactions and Dose Recommendations With Other Medicinal Products

**INTERACTIONS AND DOSE RECOMMENDATIONS WITH OTHER MEDICINAL PRODUCTS**

| Medicinal products by therapeutic areas                                          | Effect on concentration of telaprevir or concomitant medicinal product    | Clinical Comment                                                                                                                                                                                                                                                                                                                                                                                                                                                                                |
|----------------------------------------------------------------------------------|---------------------------------------------------------------------------|-------------------------------------------------------------------------------------------------------------------------------------------------------------------------------------------------------------------------------------------------------------------------------------------------------------------------------------------------------------------------------------------------------------------------------------------------------------------------------------------------|
| ANTIMYCOBACTERIAL                                                         |                                                                           |                                                                                                                                                                                                                                                                                                                                                                                                                                                                                                 |
| rifabutin                                                                        | ↓ telaprevir
↑ rifabutin                                               | Concentrations of telaprevir may be decreased, while rifabutin concentrations may be increased during co-administration. Telaprevir may be less effective due to decreased concentrations. The concomitant use of rifabutin and telaprevir is not recommended.                                                                                                                                                                                                                                  |
| BENZODIAZEPINES                                                           |                                                                           |                                                                                                                                                                                                                                                                                                                                                                                                                                                                                                 |
| alprazolam*                                                                      | ↑ alprazolam
AUC 1.35 (1.23-1.49)
C max 0.97 (0.92-1.03) | Concomitant use of alprazolam and telaprevir increase exposure to alprazolam by 35%. Clinical monitoring is warranted.                                                                                                                                                                                                                                                                                                                                                                          |
| parenterally administered midazolam*                                             | ↑ midazolam
AUC 3.40 (3.04-3.79)
C max 1.02 (0.80-1.31)  | Concomitant use of parenterally administered midazolam with telaprevir increased exposure to midazolam 3.4-fold. Co-administration should be done in a setting which ensures clinical monitoring and appropriate medical management in case of respiratory depression and/or prolonged sedation. Dose reduction for midazolam should be considered, especially if more than a single dose of midazolam is administered. Co-administration of oral midazolam with telaprevir is contraindicated. |
| zolpidem (non-benzodiazepine sedative)*                                          | ↓ zolpidem
AUC 0.53 (0.45-0.64)
C max 0.58 (0.52-0.66)   | Exposure to zolpidem was decreased by 47% when co-administered with telaprevir. Clinical monitoring and dose titration of zolpidem is recommended to achieve the desired clinical response.                                                                                                                                                                                                                                                                                                     |
| CALCIUM CHANNEL BLOCKERS                                                  |                                                                           |                                                                                                                                                                                                                                                                                                                                                                                                                                                                                                 |
| amlodipine*                                                                      | ↑ amlodipine
AUC 2.79 (2.58-3.01)
C max 1.27 (1.21-1.33) | Exposure to amlodipine was increased 2.8-fold when co-administered with telaprevir. Caution should be used and dose reduction for amlodipine should be considered. Clinical monitoring is recommended.                                                                                                                                                                                                                                                                                          |
| diltiazem
felodipine
nicardipine
nifedipine
nisoldipine
verapamil | ↑ calcium channel blockers                                                | Concentrations of other calcium channel blockers may be increased when telaprevir is co-administered. Caution is warranted and clinical monitoring of patients is recommended.                                                                                                                                                                                                                                                                                                                  |
| CORTICOSTEROIDS                                                           |                                                                           |                                                                                                                                                                                                                                                                                                                                                                                                                                                                                                 |
| Systemic dexamethasone                                                           | ↓ telaprevir                                                              | Systemic dexamethasone induces CYP3A and can thereby decrease telaprevir plasma concentrations. This may result in loss of therapeutic effect of telaprevir. Therefore this combination should be used with caution or alternatives should be considered.                                                                                                                                                                                                                                       |
| Inhaled/nasal fluticasone
budesonide                                          | ↑ fluticasone
↑ budesonide                                             | Concomitant use of inhaled fluticasone or budesonide and telaprevir may increase plasma concentrations of fluticasone or budesonide resulting in significantly reduced serum cortisol concentrations. Co-administration of fluticasone or budesonide and telaprevir is not recommended unless the potential benefit to the patient outweighs the risk of systemic corticosteroid side effects.                                                                                                  |

(Continued)

**Attachment 2: (Continued)****Interactions and Dose Recommendations With Other Medicinal Products****INTERACTIONS AND DOSE RECOMMENDATIONS WITH OTHER MEDICINAL PRODUCTS**

| Medicinal products by therapeutic areas                                                                   | Effect on concentration of telaprevir or concomitant medicinal product                                                                                                                                                    | Clinical Comment                                                                                                                                                                                                                                                                                                     |
|------------------------------------------------------------------------------------------------------------------|----------------------------------------------------------------------------------------------------------------------------------------------------------------------------------------------------------------------------------|-----------------------------------------------------------------------------------------------------------------------------------------------------------------------------------------------------------------------------------------------------------------------------------------------------------------------------|
| ENDOTHELIN RECEPTOR ANTAGONIST                                                                            |                                                                                                                                                                                                                                  |                                                                                                                                                                                                                                                                                                                             |
| bosentan                                                                                                         | ↑ bosentan                                                                                                                                                                                                                       | Concentrations of bosentan may be increased when co-administered with telaprevir. Caution is warranted and clinical monitoring is recommended.                                                                                                                                                                              |
| HIV-ANTIVIRAL AGENTS: HIV-PROTEASE INHIBITORS (PIs)                                                       |                                                                                                                                                                                                                                  |                                                                                                                                                                                                                                                                                                                             |
| Note: For this protocol, since co-infections with HIV are excluded, antiviral treatments are not allowed. |                                                                                                                                                                                                                                  |                                                                                                                                                                                                                                                                                                                             |
| atazanavir/ritonavir*                                                                                            | ↓ telaprevir
AUC 0.80 (0.76-0.85)
C max 0.79 (0.74-0.84)
C min 0.85 (0.75-0.98)
↑ atazanavir
AUC 1.17 (0.97-1.43)
C max 0.85 (0.73-0.98)
C min 1.85 (1.40-2.44) | In a drug interaction study in healthy volunteers where telaprevir was co-administered with atazanavir/ritonavir, the steady-state telaprevir exposure was reduced by 20%, while the steady-state atazanavir exposure was increased by 17%.                                                                                 |
| darunavir/ritonavir*                                                                                             | ↓ telaprevir
AUC 0.65 (0.61-0.69)
C max 0.64 (0.61-0.67)
C min 0.68 (0.63-0.74)
↓ darunavir
AUC 0.60 (0.57-0.63)
C max 0.60 (0.56-0.64)
C min 0.58 (0.52-0.63)  | In a drug interaction study in healthy volunteers where telaprevir was co-administered with darunavir/ritonavir, the steady-state telaprevir exposure was reduced by 35%, while the steady-state darunavir exposure was reduced by 40%. It is not recommended to co-administer darunavir/ritonavir and telaprevir.          |
| fosamprenavir/ritonavir*                                                                                         | ↓ telaprevir
AUC 0.68 (0.63-0.72)
C max 0.67 (0.63-0.71)
C min 0.70 (0.64-0.77)
↓ amprenavir
AUC 0.53 (0.49-0.58)
C max 0.65 (0.59-0.70)
C min 0.44 (0.40-0.50) | In a drug interaction study in healthy volunteers where telaprevir was co-administered with fosamprenavir/ritonavir, the steady-state telaprevir exposure was reduced by 32%, while the steady-state amprenavir exposure was reduced by 47%. It is not recommended to co-administer fosamprenavir/ritonavir and telaprevir. |
| lopinavir/ritonavir*                                                                                             | ↓ telaprevir
AUC 0.46 (0.41-0.52)
C max 0.47 (0.41-0.52)
C min 0.48 (0.40-0.56)
↔ lopinavir
AUC 1.06 (0.96-1.17)
C max 0.96 (0.87-1.05)
C min 1.14 (0.96-1.36)  | In a drug interaction study in healthy volunteers where telaprevir was co-administered with lopinavir/ritonavir, the steady-state telaprevir exposure was reduced by 54%, while the steady-state exposure to lopinavir was not affected. It is not recommended to co-administer lopinavir/ritonavir and telaprevir.         |

(Continued)

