## **8. PRESTUDY AND CONCOMITANT THERAPY**

The use of all therapy for hepatitis C infection (eg, Peg-IFN-alfa, RBV), prior to and during the early access program, should be recorded in the case report form (CRF).

Use of all therapy (prescription and over-the-counter) for rash and anemia administered after the first use of telaprevir until 30 days after administration of the last dose of telaprevir should be recorded on the appropriate pages of the CRF. See Section 9.3.1.1.2 for additional information on allowed and prohibited concomitant therapies for treatment of rash.

For serious adverse events, concomitant medications will be recorded in the CRF.

For therapies listed above, the therapy, start and stops dates, dosing regimen, route of administration, and dosage changes will be recorded in the CRF. All other concomitant medication should be recorded in the subject's medical record.

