### **Recommendations for Other Medicinal Products**

Recommendations for other medicinal products, as a result of drug interactions with telaprevir, are provided in Attachment 2. These recommendations are based on either drug interaction studies or predicted interactions due to the expected magnitude of interaction and potential for serious adverse events or loss of efficacy. Attachment 2 is a comprehensive list of all recommendations, however, since co-infections with active hepatitis B and HIV are excluded, antiviral treatments are not allowed.

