#### **9.3.1.1.2. Rash Treatment**

Antihistamines and topical corticosteroids may provide symptomatic relief to subjects who develop rash and experience associated symptoms such as pruritus.

Treatment of rash throughout the treatment period of the early access program should always follow generally accepted medical standards. In addition, the following treatment recommendations during telaprevir dosing should be followed.

Permitted topical and systemic antihistaminic drugs allowed for use with caution for all grades of rash include diphenhydramine (Benadryl®), hydroxyzine, levocetirizine (Xyzal®), and desloratadine (Clarinex®). Subjects should be followed symptomatically for possible increased exposure and worsening of adverse events such as drowsiness, and should be advised not to drive or operate heavy machinery while receiving antihistamines. The following antihistamines are prohibited from Day -14 until 7 days after the last dose of telaprevir: astemizole, terfenadine, and loratadine (see Section 8 and Attachment 2).

Because immunosuppression due to systemic corticosteroids can cause elevations in HCV RNA levels and because of the suspected drug-drug interactions between telaprevir and systemic corticosteroids, the latter should be used only when clinically necessary and after other treatments and measures have been employed, when possible. A consultation with a dermatologist should be requested for advice if needed. Telaprevir, Peg-IFN-alfa, and RBV must be discontinued immediately and permanently if a subject receives treatment with systemic corticosteroids (see also Section 10.2).

Topical corticosteroid use is permitted, but should be limited to brief periods, eg, up to 2 weeks of continuous/regular use, and limited to use on up to 50% of the body surface. Cream or lotion preparations are strongly encouraged in this situation, due to a lower absorption potential. Use of gel or ointment preparations of topical corticosteroids is discouraged due to a relative higher absorption potential. Treatment of skin eruptions with investigational agents or use of approved drugs in an off-label manner is also discouraged.

Use of all therapy (prescription and over-the-counter) for rash administered after the first use of telaprevir until 30 days after administration of the last dose of telaprevir, should be recorded on the appropriate pages of the CRF.

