#### **9.3.1.1.3. Rash Management**

All skin events should be evaluated together with other systemic symptoms and laboratory abnormalities.

Management of rash until 30 days after the last telaprevir dose (Week 16 or earlier) should follow generally accepted medical standards, taking into account the protocol defined procedures described hereafter and treatment recommendations during telaprevir dosing described in Section 9.3.1.1.2. Management of rash during the subsequent weeks of treatment (standard treatment) should be in accordance with prescribing information recommendations for Peg-IFN-alfa and RBV.

Note that subjects having a skin rash (any grade) that requires treatment with systemic corticosteroids must have telaprevir, Peg-IFN-alfa, and RBV discontinued immediately and permanently. The sponsor's physician responsible for the early access program should be notified immediately of any subject who has a skin rash that requires treatment with systemic corticosteroids. The rash pages in the CRF must be completed.

Subjects experiencing any skin reaction considered to be a serious adverse event during telaprevir administration must permanently discontinue telaprevir treatment.

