### **10.2. Discontinuation of Treatment**

If a subject's study treatment (telaprevir) must be discontinued before the end of the treatment regimen, this will not result in automatic withdrawal of the subject from the early access program.

A subject's treatment (telaprevir, Peg-IFN-alfa, RBV) may be discontinued if:

1. an serious adverse event occurs  
(Note: treatment must be discontinued for skin reactions considered serious adverse events, as described in the table below);
2. they fail to comply with the protocol requirements or fail to cooperate with the investigator.

A subject's treatment with telaprevir may be permanently discontinued if a subject develops a medical condition that requires concomitant therapy with a prohibited drug listed in Section 8.

Subjects must discontinue telaprevir and Peg-IFN-alfa/RBV or have their treatment modified for the reasons included in the table below.

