| Grade 3 or 4 adverse event/toxicity at least possibly related to telaprevir, except for grade 3 elevations in ALT/AST, grade 3 or 4 GGT elevations, and grade 3 or 4 hemoglobin decreases (unless they are persistent) | 
 
• Permanently discontinue telaprevir and continue Peg-IFN-alfa and RBV.
 
• Permanently discontinue telaprevir and interrupt RBV or RBV and Peg-IFN-alfa if clinically indicated.
 
• Peg-IFN-alfa and/or RBV may be restarted if there is improvement in the adverse event/toxicity within 14 days following the interruption. RBV monotherapy is not allowed.
 
                                                                                                                                                                     |
| Treatment with systemic corticosteroids                                                                                                                                                                                | 
 
• Permanently discontinue telaprevir, Peg-IFN-alfa, and RBV immediately.
 
                                                                                                                                                                                                                                                                                                                                                                                                                                                                          |
| Grade 3 rash (for DRESS, EM, and AGEP, see special instructions below)                                                                                                                                                 | 
 
• Permanently discontinue telaprevir immediately and continue Peg-IFN-alfa and RBV.
 
• Interrupt RBV if the rash does not improve within 7 days after telaprevir discontinuation and continue Peg-IFN-alfa unless interruption is medically indicated. The investigator may also discontinue telaprevir, Peg-IFN-alfa, and RBV simultaneously if clinically indicated.
 
• Peg-IFN-alfa and/or RBV may be restarted if there is improvement in the rash within 14 days following the interruption. RBV monotherapy is not allowed.
 
 |

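### Attachment 2 lets systemic dexamethasone be given with telaprevir with caution, while Section 10.2 requires a permanent stop of all three drugs on any systemic corticosteroid

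*Protocol*

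**What the plan says.** Four places in the protocol bear on the point.

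- **Attachment 2, Corticosteroids, systemic dexamethasone row.** Dexamethasone induces CYP3A and may weaken telaprevir. The advice is: "Therefore this combination should be used with caution or alternatives should be considered". The row does not mention stopping any drug.
- **Section 10.2, Discontinuation of Treatment.** The table is introduced by: "Subjects must discontinue telaprevir and Peg-IFN-alfa/RBV or have their treatment modified for the reasons included in the table below". For treatment with systemic corticosteroids the single listed action is: "Permanently discontinue telaprevir, Peg-IFN-alfa, and RBV immediately". A note to the table bars restarting telaprevir once it has been stopped under one of these criteria.
- **Section 9.3.1.1.2, Rash Treatment.** Telaprevir, Peg-IFN-alfa and RBV "must be discontinued immediately and permanently if a subject receives treatment with systemic corticosteroids", with a cross-reference to Section 10.2.
- **Section 9.3.1.1.3, Rash Management.** Subjects with a "skin rash (any grade) that requires treatment with systemic corticosteroids must have telaprevir, Peg-IFN-alfa, and RBV discontinued immediately and permanently".

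**The concern.** An investigator who wants to give systemic dexamethasone to a subject on telaprevir, for a reason other than rash, gets two different answers. Attachment 2 reads as though treatment can continue under caution. Section 10.2 says all three drugs end at once.

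The second course cannot be undone for telaprevir. The first leaves a subject on drugs that a mandatory rule says must be stopped. The population has severe fibrosis or cirrhosis and, in the protocol's own account in Section 3.2.1, few other options, so an error either way matters to the subject concerned. Sites may also handle like subjects differently, and the discontinuation dates and reasons entered on the CRF under Section 10.2 would follow whichever text the site had read.

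**Working it through.** There is no figure to reproduce and no arithmetic; the check is a comparison of texts.

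1. **Does one subject fall under both texts?** Yes. Attachment 2 lists systemic dexamethasone under its corticosteroid heading, and the Section 10.2 row covers systemic corticosteroids as a class.

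2. **How wide is the Section 10.2 row?** It names no agent, dose, duration or indication. It stands apart from the rows for grade 3 rash, for DRESS, EM and AGEP, and for grade 4 rash, so it is not a sub-item of rash. The sentence in Section 9.3.1.1.2 sits in a rash section, but its condition is that the subject receives the steroid, whatever the reason. Only the sentence in Section 9.3.1.1.3 is worded for rash alone.

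3. **Does any text rank the two?** Section 8 calls Attachment 2 "a comprehensive list of all recommendations, however, since co-infections with active hepatitis B and HIV are excluded, antiviral treatments are not allowed". Antivirals are the one override stated there. The Section 8 list of drugs that should not be prescribed does not name corticosteroids. Its pointer to the rash section is confined to rash: "See Section 9.3.1.1.2 for additional information on allowed and prohibited concomitant therapies for treatment of rash". No sentence says that Section 10.2 prevails over Attachment 2.

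4. **What follows in each situation?**

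| Situation | Attachment 2 | Sections 9.3.1.1 and 10.2 | Result |
|---|---|---|---|
| Systemic dexamethasone for rash, on telaprevir | Caution or alternatives | Stop 3 drugs permanently | Settled by the explicit rash rule in Section 9.3.1.1.3 |
| Systemic dexamethasone for another reason, on telaprevir | Caution or alternatives: 0 drugs stopped | Stop 3 drugs permanently | Open conflict |
| Systemic dexamethasone after telaprevir has ended | Silent, since it covers interactions with telaprevir | Row has no time limit | No conflict between the two texts |

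The live conflict is therefore the second row of the table, within the planned 12 weeks of telaprevir.

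**The case against.** The best defence is that the two texts differ in rank. Section 10.2 says must; Section 8 and Attachment 2 itself call the attachment's contents recommendations. The dexamethasone row never requires telaprevir to continue, and one of its two options is to look for an alternative. A site that avoids dexamethasone, or gives it and stops treatment under Section 10.2, breaches nothing. Section 6 also sends sites to Section 10.2 for further rules on stopping. All of this stands: a careful site can reach the stricter answer, and it would be too strong to infer that no site could comply with both texts. It does not remove the problem, because the row read alone implies that treatment may go on, and the ranking is left to the reader.

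A second defence is that the stop was meant for rash only. That is a possible intent, given where Section 9.3.1.1.2 sits and how Section 9.3.1.1.3 is worded. But then the Section 10.2 row is too broad, and it would end three drugs in subjects for whom no stop was intended. One text needs correcting on either reading.

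A third is that the scope is small. Exclusion criteria 13, 14 and 17 keep out subjects with immunologically mediated disease, functionally limiting chronic lung disease, and most functioning organ grafts. This plausibly removes several reasons for systemic steroids. That also stands.

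Two further inferences are tempting and should not be drawn:

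- A reader might take the absence of a prohibition in the dexamethasone row as deliberate permission, because other rows state theirs. Attachment 2 does not support this. Its wording is graded (domperidone is to be avoided; rifabutin and salmeterol are not recommended), and it has not been fully aligned with the protocol: it still carries dosing advice on immunosuppressants although most functioning grafts are excluded.
- A reader might argue that Section 9.3.1.1.2 shows the stop was meant for every indication, because "immunosuppression due to systemic corticosteroids can cause elevations in HCV RNA levels" whatever the steroid is for. That section gives a second reason as well, a suspected interaction between the drugs, which is the kind of reason Attachment 2 gives. Both reasons introduce advice to hold steroids back until other measures have been tried. They do not show which scope was intended.

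**Conclusion.** The inconsistency is real and should be corrected. It is confined to systemic dexamethasone given for a reason other than rash during telaprevir dosing. For such a subject the texts differ between stopping no drug and permanently stopping three.

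The conclusion rests on reading the Section 10.2 row as it is worded, without a limit by indication, and on the lack of any precedence statement. The protocol gives no frequency of systemic dexamethasone use, so the number of subjects affected is unknown and may be small. A reader might go on to infer damage to the safety estimates; the documents do not support that. Nothing here changes the planned sample size, the precision table in Section 11.4 or the descriptive analysis. The point concerns subject safety and uniform handling across sites.

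**What to change.** Reword the systemic dexamethasone row in Attachment 2 to say that treatment with a systemic corticosteroid requires permanent discontinuation of telaprevir, Peg-IFN-alfa and RBV under Section 10.2. Add one sentence, in Section 8 or at the head of Attachment 2, that Sections 8, 9.3.1.1 and 10.2 prevail where the attachment differs.

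If the sponsor intended the stop for rash only, leave the dexamethasone row as it is for other uses, and limit both the Section 10.2 row and the corresponding sentence in Section 9.3.1.1.2 to steroids given for rash. The sponsor has to say which was meant; the protocol does not settle it.

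The cost of the first option is one table row and one sentence in an amendment, with a letter to sites. Neither option touches sample size or analysis.
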